#### Primary outcome analyses

We will assess the efficacy of an IES system added to the standard care versus standard wound care on sacral and ischial pressure injury scores measured over time using a generalized mixed effects ordinal regression cumulative logit model which considers treatment and time (categorical) as fixed effects and subject as a random effect and accounts for (1) the ordinal nature of the data and (2) the within-subject correlation over time. The model will allow differing number of measurements and lengths of follow-up for patients but will assume that shorter follow-up or dropout is largely at random and not due to either improvement or worsening of SPI symptoms. We will also assess the treatment-by-time interaction to assess whether the treatment effect is consistent over time. Given a significant interaction, we will assess the treatment effect at various time points, although the primary analysis will be the treatment effect collapsed over time.

Results will be reported as a proportional odds ratio which estimates the odds of an IES-treated patient having a higher (worse) score than a randomly chosen standard care patient. For example, an odds ratio of 0.6 would mean the treatment was associated with an estimated 40% lower odds of an EIS-treated patient having a higher score compared to standard care; correspondingly, a treated patient has a 40% higher odds of having a lower (better) score compared to a standard care patient.

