### Randomization and blinding

Randomization sequences will be generated using the PLAN procedure in the SAS statistical software and will be stratified by clinical site and initial pressure injury stage at point of consent (stage I or II). Furthermore, random sized blocks will be used. Study personnel will randomize patients after enrollment via a central 24-h Interactive Web Randomization System (REDCap). This is an open label study, so no blinding is required. Randomization codes will be maintained until after all the data are collected and analyzed. The patient and study staff will be informed of the randomized allocation.

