#### Significance level

The significance level will be 0.05 for all hypothesis testing and will be controlled at 5% across any multiple comparisons using appropriate multiple testing procedures. Two-sided tests for superiority will be used throughout.

For the statistical analysis of clinical course, unstageable injuries will be assigned a score of 3 (equivalent to stage III injuries). If a patient experiences multiple sacral/ischial pressure injury simultaneously, the most severe injury will be used for analysis.

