#### Primary outcome

The primary outcome will be sacral and ischial pressure injury assessed with the SPI instrument score (range 0–4) over time. For the statistical analysis of clinical course, unstageable injuries will be assigned a score of 3 (equivalent to stage III injuries). For ulcers that progress to deep tissue injuries (DTI), these will be assigned a score of the previous ulcer stage plus one. If a patient experiences multiple sacral/ischial pressure injury simultaneously, the most severe injury will be used for analysis. The primary outcome will be based on the combined stage 1 and stage 2 ulcer types.

Patients will be assessed twice daily by the bedside nurse for pressure injury location and stage from study entry to discharge from the hospital or at least 30 days, whichever comes first. This is a standard wound care evaluation protocol for nursing. Wound care nursing specialist consultation staging will be used instead of bedside nursing staging should a discrepancy occur. If SPI scores are available after discharge and within the 30 days, those data will be included in the analyses as well, even if the SPI are healed or at the worst stage.

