### Sample size considerations

Sample size calculations are based on the primary outcome of pressure ulcer score (0–4), measured over time within a patient and assuming a statistical model (mixed effects ordinal regression) which accounts for the within-subject correlation over the repeated measurements. We designed the study to have 90% power at the 0.05 significance level to detect a treatment effect as large or larger than the effect seen in Table 1 (A) (for the combined starting stages I and II). Sample size was estimated based on applying a design effect to a standard 2-group comparison for independent data (i.e., the Wilcoxon Rank Sum test); it incorporates the number of measurements per patient (m) and an assumed intraclass correlation (ICC) to account for within-subject correlation (i.e., multiply standard sample size calculation by 1 + (m-1)ICC) [15].

**Table 1 Tab1:** Minimal clinically important differences in pressure ulcer score

**A. Combined stages I and II** ***N***** = 586 fixed, *****assuming single measurement***** per patient** ***N***** = 668 with interim analysis adjustment**	**Pressure ulcer score (row percent)**				
	**0**	**I**	**II**	**III**	**IV**
**Intervention**	**82.5**	**2.5**	**12.5**	**2.5**	**0**
**Control**	**72.5**	**2.5**	**15**	**5**	**5**

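### The primary model leaves out site and starting stage, on which randomization is stratified; adding them is free, with a gain from negligible to material

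*Protocol article*

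**What the plan says.** Under Randomization and blinding, the sequences "will be stratified by clinical site and initial pressure injury stage at point of consent (stage I or II").

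Under Primary outcome, the endpoint is "sacral and ischial pressure injury assessed with the SPI instrument score (range 0–4) over time", and "The primary outcome will be based on the combined stage 1 and stage 2 ulcer types". When a patient has several sacral or ischial injuries, the worst one is scored. Scoring begins at study entry.

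Under Primary outcome analyses, the article names the terms of the model: a generalized mixed ordinal regression "which considers treatment and time (categorical) as fixed effects and subject as a random effect". The treatment effect collapsed over time is primary.

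Baseline information is used elsewhere. Treatment effect heterogeneity tests interactions with baseline factors listed in an additional file. The Discussion promises a treatment-by-stage interaction and separate estimates per stage. Missing data methods puts the baseline variables into the imputation models. None of these puts stage or site into the model that yields the primary odds ratio.

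**The concern.** Factors used to stratify randomization are normally carried into the analysis. Balancing the arms on a prognostic factor reduces the true sampling variation of the treatment contrast. A model without that factor does not know this, so its standard error is too large and its test too cautious.

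Here one of the two factors is also a baseline measure of the 0–4 outcome itself. Twice-daily scoring from entry means that early scores will often repeat the entry stage until the ulcer heals or worsens. The subject random effect does not remove this difference. Treatment is constant within a patient, so it is tested against between-patient variance, and a stage difference left out of the fixed effects stays in that variance.

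At stake are the precision of the primary odds ratio and the power of the test, at the final analysis and at the interim looks, which use the same outcome. The validity of the test is not at stake.

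**Working it through.** **1. The plan's own sample size.** Inputs are Table 1 A (intervention 82.5/2.5/12.5/2.5/0, control 72.5/2.5/15/5/5), two-sided 0.05 and 90% power. The probability that a control patient scores worse than a treated patient, counting ties as one half, is 0.55625. With pooled category proportions p̄, the tie-corrected Wilcoxon total is

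N = (1.960 + 1.282)² × (1 − Σp̄³) / [3 × (0.55625 − 0.5)²] = 10.507 × 0.5318 / 0.009492 = 588.7.

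Other variance conventions give 583.6 and 584.5, so the stated 586 is reproduced. Taking the stated 668 with interim looks, and applying the instruction to "multiply standard sample size calculation by 1 + (m-1)ICC" and then dividing by m, gives 668 × (1 + 9 × 0.8)/10 = 547.8, which is the stated 548. No covariate enters anywhere, so the 90% does not rely on adjustment.

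**2. What Table 1 implies about stage.** The only figures that link starting stage to the score are the hypothetical rows of Table 1 B and C, and Table 1 A is their exact average. Averaged over arms, the mean score is (0.275 + 0.600)/2 = 0.4375 for a stage I start and (0.425 + 0.750)/2 = 0.5875 for a stage II start. The between-stage variance is (0.15/2)² = 0.005625 and the total variance is 1.0498, so stage explains 0.005625/1.0498 = 0.54% (0.45% on the rank scale). Simulated power from these rows, without and with stage in a proportional-odds model, was 89.3% and 89.7% at N = 588, and 92.3% and 92.5% at N = 668.

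**3. If stage predicts more than Table 1 shows.** Suppose the covariates explain a share R² of the variance that matters and the adjusted model has 90% power. The unadjusted model then has power Φ[(1.960 + 1.282) × √(1 − R²) − 1.960].

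| R² (assumed) | Unadjusted power |
|---|---|
| 5% | 88.5% |
| 10% | 86.8% |
| 20% | 82.6% |
| 30% | 77.4% |

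**4. The planned type of model.** Random-intercept cumulative-logit data were simulated with 548 patients, 10 assessments, a latent ICC of 0.8 and 400 trials per row. The Monte Carlo error is 1 to 2 points for each power. The effect was set to 0.8 of the Table 1 A effect on the latent scale. At the full effect (300 trials per setting) both versions had at least 97% power in this set-up and differed by at most 1.3 points.

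| Share of between-patient variance due to stage (assumed) | Without stage | With stage |
|---|---|---|
| 0.5% | 86.0% | 86.5% |
| 17% | 87.0% | 91.0% |
| 47% | 91.5% | 97.2% |

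**5. If early scores repeat the entry score.** Two illustrations, both resting on assumptions that are not in the article:

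- Each patient stays at the starting stage and moves once, at a uniformly distributed time, to a Table 1 B or C category (548 patients, 10 assessments, 150 trials, Monte Carlo error about 3.5 points). Power was 74% without stage and 85% with it. The mean likelihood-ratio chi-square rose from 7.6 to 10.0. With all movement in the first third of follow-up, the gain in information falls to about 8%.
- The planned ICC also holds between the entry score and follow-up. In a linear approximation, adjusting for the entry score multiplies the variance by 1 − m·ICC²/[1 + (m − 1)·ICC]. With m = 10 this is 0.86, 0.55 and 0.22 for ICC 0.2, 0.5 and 0.8. The factor is optimistic, because eligibility restricts most entry scores to 1 or 2.

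**6. Size of the test with no treatment effect.** In the step 4 set-up with stage at 47%, rejection was 1.7% without stage and 5.0% with it (300 trials, Monte Carlo error about 1.3 points). With stage at 0.5%, both gave 2.3%, so these runs are imprecise. A regression on subject means under the uniform-movement assumption (4,000 trials) gave 3.3% and 4.9%. Where stage is prognostic, both comparisons point to a conservative unadjusted test.

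**The case against.** The article condenses a longer protocol, covariate terms are often settled in an analysis plan, and the model sentence does not claim to be complete. The planned 90% comes from an unadjusted calculation, so adjustment repairs nothing in the design. The unadjusted test stays valid. The effect within each stage will be reported in any case. The only figures in the article that bear on stage imply almost no gain.

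Most of this stands, and it limits the claim. It does not remove it: the article lists the fixed and random effects explicitly, and the list does not match the stratification it describes.

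A reader might infer four stronger things that the article does not support:

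- *That a substantial power loss is established.* The 74% against 85% contrast depends on an assumed path of healing. Other paths give little or nothing.
- *That the 90% power is wrong.* It was derived without covariates and reproduces.
- *That type I error is inflated.* The direction is the opposite.
- *That every series starts at 1 or 2, so the stratum equals the baseline score.* Trial population admits patients with additional higher-stage injuries, and the worst sacral or ischial injury is scored, so the entry score can exceed the stratum.

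Equally, the near-zero case should not be taken as the expected one. Table 1 puts 70% to 85% of patients at score 0, whereas entry requires a stage 1 or 2 injury. Entry and early scores therefore cannot follow Table 1.

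**Conclusion.** The stated primary model omits both stratification factors, and with them a baseline measure of the outcome. Where stage or site is prognostic, the analysis is conservative and less precise than it need be.

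The size depends on a baseline-to-follow-up correlation that the article does not state. The gain from adjustment is under 1 power point if scores follow Table 1 B and C throughout. It is about 4 to 6 points in simulations where stage explains 17% to 47% of between-patient variance and unadjusted power is about 87% to 92%. It could be larger if early scores largely repeat the entry score. Nothing in the article allows a figure for site; the case for site rests on matching the randomization.

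This is a free improvement, not an error that invalidates the design.

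**What to change.** - Add the stage stratum (I or II) and site to the primary mixed model. Site may be fixed or random; with the three centers reported so far, fixed is simpler.
- Put the same terms into the GEE alternative, and stratify or adjust the Cox models by them.
- Include the entry SPI score, defined by the worst sacral or ischial injury, as a baseline covariate, and state that the entry assessment is not a response.
- Use the same model at the interim looks.
- Record that the choice was made without access to comparative results. The trial is open label, and the first interim analysis was expected in January 2024.

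The cost is a change of wording. Site and starting stage are already recorded at randomization and scoring begins at entry, so no new data are needed. The sample size calculation can stay as it is.

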### Alternative statistical models and sensitivity analyses

First, if the generalized mixed effects model does not converge or is deemed not sufficient, an analogous generalized estimating equation (GEE) model will be used in which the correlation is adjusted for using the R matrix (within-subject correlation), either unstructured or autoregressive (AR (1)). Second, a recurrent time to event model with ordinal outcome (the continuation ratio approach) [14] will be fit. This approach models the risk for the *j*th event (e.g., a certain category of pressure injury at a specific f/up measurement) ignoring any previous events, but accounting for subject as random effect, and can be modeled using an event- stratified proportional hazards regression model.

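### The primary odds ratio is misread: 0.6 means 67%, not 40%, higher odds of a better score, and it is not the odds of scoring worse than a random control patient

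*Protocol article*

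**What the plan says.** Under Primary outcome analyses, the protocol article specifies a "generalized mixed effects ordinal regression cumulative logit model which considers treatment and time (categorical) as fixed effects and subject as a random effect". The outcome is the pressure injury score from 0 to 4, with higher meaning worse.

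The same section gives the reporting rule in two parts:

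- **Definition.** The result is "a proportional odds ratio which estimates the odds of an IES-treated patient having a higher (worse) score than a randomly chosen standard care patient".
- **Worked example.** The section states that "an odds ratio of 0.6 would mean the treatment was associated with an estimated 40% lower odds" of a higher score. It then presents as equivalent that "a treated patient has a 40% higher odds of having a lower (better) score compared to a standard care patient".

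If the mixed model fails to converge or is judged inadequate, Alternative statistical models and sensitivity analyses says that "an analogous generalized estimating equation (GEE) model will be used". The section on displaying results carries the ORs into a forest plot over time and an aggregate OR.

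**The concern.** The two halves of the worked example describe different effects. A 40% fall in the odds of a worse score is not a 40% rise in the odds of a better one.

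The definition describes a comparison between two patients drawn one from each arm. The model estimates something else: a ratio of two arm-level odds at a cut-point of the score. Most patients are expected at score 0, so tied pairs dominate and the two quantities are well apart.

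A report that followed this section would give a wrong percentage in the better direction and attach a wrong meaning to the primary estimate. Because the model has a subject random effect, its OR is also conditional on the subject, which is a further step away from a comparison with a randomly drawn patient.

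**Working it through.** **Inputs.** The example OR of 0.6 comes from Primary outcome analyses. The score distributions come from Table 1 (A), for scores 0, I, II, III, IV:
- Intervention: 82.5, 2.5, 12.5, 2.5, 0%
- Control: 72.5, 2.5, 15, 5, 5%

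**1. Reversing the OR (exact, no assumptions).**
- Lower odds of a worse score: 1 − 0.6 = 0.40. The stated 40% reproduces.
- Higher odds of a better score: 1/0.6 = 1.667, so 67% higher at every cut-point. The stated 40% does not reproduce.
- A 40% increase would need an OR of 1/1.4 = 0.714.

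**2. Cut-point OR against the pairwise quantity, Table 1 (A).**
- OR for a score above 0: (0.175/0.825)/(0.275/0.725) = 0.2121/0.3793 = 0.559.
- P(IES worse) = 0.025×0.725 + 0.125×0.75 + 0.025×0.90 = 0.134.
- P(tie) = 0.825×0.725 + 0.025×0.025 + 0.125×0.15 + 0.025×0.05 = 0.619.
- P(IES better) = 1 − 0.134 − 0.619 = 0.247.
- Odds of being worse, ties split: (0.134 + 0.309)/(0.247 + 0.309) = 0.80.

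**3. The same check with an OR of exactly 0.6.** Multiply the control odds of exceeding each cut-point by 0.6. The OR is then 0.60 by construction.

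| Quantity | Value |
|---|---|
| P(IES worse) | 0.149 |
| P(IES better) | 0.241 |
| P(tie) | 0.610 |
| Literal odds of being worse, 0.149/0.851 | 0.176 |
| Worse-to-better ratio, ties dropped | 0.621 |
| Odds of being worse, ties split | 0.833 |

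None equals 0.60.

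**4. The definition under no effect.** Give both arms the control distribution. Then P(worse) = (1 − sum of squared proportions)/2 = (1 − 0.55375)/2 = 0.223. The literal odds of being worse are 0.223/0.777 = 0.29, whereas an OR under no effect is 1.

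**5. Conditional and population-averaged ORs (illustration only).** Assume a normal random intercept and an intraclass correlation (ICC) on the latent logistic scale, with variance σ² = ICC/(1 − ICC) × π²/3. The usual approximation is: population log OR = ln(0.6)/√(1 + 0.346σ²). A conditional OR of 0.60 then corresponds to about:
- 0.64 at ICC 0.2
- 0.71 at ICC 0.5
- 0.81 at ICC 0.8

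The protocol does not say that its ICC is on this scale. Under Sample size considerations the ICC enters a design effect applied to a Wilcoxon calculation. The direction (population OR nearer 1) does not depend on that; the sizes do.

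**The case against.** The faults lie in one explanatory sentence and the second half of one example. The main reading, 40% lower odds of a worse score, is right. The OR and its interval would be estimated correctly whatever this text says, and the planned display of score distributions by arm lets readers see the effect directly. All of this stands, and it limits the severity. A generous reader could also take the definition to mean the worse-to-better ratio with ties dropped. That comes close (0.62 against 0.60), but it is not what the sentence says and it is still not equal.

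A reader might infer more than the document supports:

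- **That the benefit would be exaggerated.** The slip goes the other way: 40% understates the 67%.
- **That the GEE fallback contradicts the primary model.** Calling it analogous is naturally read as the same outcome and link with the correlation handled differently. It does not claim equal coefficients. Under the random-intercept model the conditional OR is 1 exactly when the population OR is 1, so the null hypothesis is shared. The OR's size would differ on fallback, which calls for labelling.
- **That the headline must become a population-averaged OR.** A subject-specific OR is a legitimate target of the model, which the protocol names openly. Changing it is a trade-off: unweighted GEE needs a stricter missing-data assumption than the likelihood model, and the protocol relies on dropout being largely at random.
- **That the plan's own effect converts to a particular conditional OR.** Table 1 (A) has no single proportional OR; its four cut-points give 0.56, 0.53, 0.23 and 0. Any conversion rests on a chosen cut-point as well as the assumed latent ICC.

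**Conclusion.** The reporting rule is wrong as written on two counts. First, an OR of 0.6 means 1.67 times the odds of a better score, so 67% higher and not 40%; this is exact. Second, the OR is not the odds of scoring worse than a randomly drawn control. On the protocol's Table 1 (A) the figures are 0.56 at 0 versus above 0, against 0.80 pairwise with ties split. The comparison uses the planning distributions only, and nothing elsewhere in the article repairs the text.

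The model, test, significance level, sample size and headline estimand are unaffected. This is a lower-severity correction, worth making because the text governs how the primary effect will be described. The subject-specific nature of the OR needs a label only, and the conditional-to-marginal figures are illustrations under an assumed latent-scale ICC.

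**What to change.** Under Primary outcome analyses:

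- **Replace the definition.** Suggested text: the proportional odds ratio is the ratio of the odds, IES to standard care, of a score above any given cut-point, conditional on the subject random effect.
- **Replace the example.** Suggested text: an odds ratio of 0.6 means 40% lower odds of a worse score or, equivalently, 67% higher odds of a better score (1/0.6 = 1.67).
- **Label the estimates.** Call the mixed-model OR subject-specific, and call any OR from the GEE fallback population-averaged, so that the two are not read as the same quantity.
- **Pairwise statement only if wanted.** If the authors wish to say something about a randomly chosen patient, report win odds with the handling of ties stated. Otherwise drop the phrase.

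The cost is a text edit, plus one extra calculation if win odds are added. No design change or new data are needed.

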#### Missing data methods

Study personnel will go to great lengths to avoid missing outcomes data. In any case, missing data in the analyses will be assessed using multiple imputation with chained equations (MICE, also known as fully conditional specification) [13], in which predictions for missing data points will be made using regression models containing all available baseline and outcome variables. We will use 100 MICE iterations and then average predictions for missing values. Using this methodology, even data that is originally missing not at random (MNAR) may effectively be missing at random (MAR) since the predictions utilize information from many variables which might represent the reason(s) for missingness.

#### Displaying of results/treatment effect

We will display the distribution of scores for treatment and control over time. We will also display a forest plot of odds ratios over time and the cumulative/aggregate odds ratio collapsed over time.

